#### Feasibility of the intervention and delivery

This will be evaluated by keeping record of whether the Ca-GBBB is delivered, received and enacted as intended. We will also keep records of each session duration, and collect feedback about administration and suitability of the intervention components for each session through a feedback form.

#### Acceptability and tolerability of the intervention

Acceptability is defined as “the extent to which the therapist delivering the intervention and the participants receiving the intervention consider it to be appropriate” [17].

Tolerability is defined as “the ability to endure the intervention” [18].

These aspects will be assessed as participant satisfaction with the Ca-GBBB intervention that is operationalized by the:(i)Record of the number of sessions completed by each participant (*The criterion for acceptability is a mean attendance rate of* > *50% i.e. at least 8 sessions*).(ii)Total duration of each session.(iii)Participants’ feedback on the assessment and intervention maintained through the feedback forms and therapist session logs.(iv)Participant satisfaction with the intervention assessed with the Client Satisfaction Questionnaire (CSQ) [19].(v)In-depth semi-structured interviews with participants completing the intervention and participants not attending the session.

### Outcome assessment measures

The following assessments will be completed at baseline and 4-month post-randomization (i.e., end of intervention) (See Fig. 2 SPIRIT Flow Diagram).

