*(GBBB)* [12], has been found to be feasible and acceptable for patients with BN in Japan [13]. This intervention consists of 16 weekly sessions and has been tested widely in clinical trials [14]. To the best of our knowledge the evidence on psychological management of EDs in LMICs is limited, and it is non-existent in Pakistan. Therefore, the aim of this mixed method feasibility Randomized Controlled Trial (fRCT) is to explore the feasibility and acceptability of therapist delivered, manualized culturally adapted-GBBB (Ca-GBBB) intervention for individuals who screen positive on measures of BN and BED in Pakistan.

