### Procedure

Ethics permission for the trial was sought from the National Bioethics Committee (NBC) of Pakistan (Ref: No.4-87/NBC-669/21/400). The trial is registered at clinicaltrials.gov (NCT05724394). Individuals who wish to participate in the study and are ready to sign informed consent will complete the consent process for screening (see Fig. 1 Trial Flow Chart). A trained researcher will assess the eligibility of the participants by using the study eligibility checklist. As part of eligibility assessment, the researchers will administer the BEDS-7 to screen for BED and the BITE to screen for BN. Eligible participants will be given a PIS and the purpose of the trial will be explained. All potential participants will have the opportunity to ask for more details about the study. Written consent will be obtained from all eligible participants who are willing to participate. Baseline assessments of consented participants will be conducted by the researchers trained in the Good Clinical Practice (GCP) who will administer study questionnaires. Assessments will be completed either face to face at a research office or recruiting health facility, or online over a telephone call or via Zoom link, depending on participant’s convenience. After completing baseline assessments, participants will be randomized into one of the two trial arms. Participants will be informed about the status of their allocated study arm within 1 week of randomization. Participants in the intervention arm will receive sessions of Ca-GBBB for a period of 16 weeks. Follow up assessment will be completed of all the participants regardless of their treatment arms at 16th week post-randomization. The assessments will take 45–60 min to complete.

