Participants’ convenience will be considered while deciding the time and venue of the sessions. Intervention will be delivered in weekly sessions over four months, and each session will last for 45–50 min. Special consideration will be given to the cultural adaptation of the content i.e. phrases of the manual while translating it into Urdu. Moreover, culturally relevant cases will be integrated, and a shared understanding will be aimed to address cultural aspects (gender roles and financial challenges etc.).

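### The single follow-up at week 16 after randomisation is labelled end of intervention, but a 16-week course that may start a week after randomisation ends up to a week later

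*Protocol article*

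**What the plan says.** All statements are in the protocol article.

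- **Notice of allocation (Procedure):** "Participants will be informed about the status of their allocated study arm within 1 week of randomization".
- **Length of treatment (Procedure):** "Participants in the intervention arm will receive sessions of Ca-GBBB for a period of 16 weeks".
- **Length of treatment (Culturally adapted Getting Better Bite by Bite):** "Intervention will be delivered in weekly sessions over four months". The same paragraph says that participants' "convenience will be considered while deciding the time and venue of the sessions".
- **Number of sessions (Background):** for the parent manual, "This intervention consists of 16 weekly sessions". The attendance criterion under Acceptability and tolerability, "50% i.e. at least 8 sessions", implies the same total for the adapted version.
- **Follow-up (Procedure):** "Follow up assessment will be completed of all the participants regardless of their treatment arms at 16th week post-randomization".
- **Follow-up (Outcome assessment measures):** "The following assessments will be completed at baseline and 4-month post-randomization (i.e., end of intervention".

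No later assessment is described. The text gives no maximum time from notice of allocation to session 1.

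**The concern.** Three times in the Procedure section have to agree for the end-of-intervention label to be true: when treatment can start, how long it runs, and when everyone is assessed. Treatment length and assessment time are both 16 weeks. The assessment clock starts at randomisation, whereas treatment cannot start until the participant knows the allocation. Any delay between the two puts the assessment before the end of the treatment period by the same amount.

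This matters because it is the only post-baseline measurement. Under Objectives and Quantitative analysis, its data help decide which measure becomes the primary outcome of the full trial, which measures are sensitive to change, and how large that trial should be. The CSQ-8 is among the assessments scheduled then and is one of the listed acceptability measures. If some intervention participants have finished and others have not, their change scores, spread and satisfaction mix complete and incomplete courses under a label that says all are complete.

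**Working it through.** **Inputs.** Delay to notice of allocation: 0 to 7 days (Procedure). Treatment period: 16 weeks = 16 × 7 = 112 days (Procedure). Planned sessions: 8 / 0.50 = 16 (Acceptability and tolerability), matching the Background. Assessment: day 112 (Procedure), or 4 months = 4 × 365.25/12 = 121.75 days = 17.4 weeks (Outcome assessment measures).

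**The plan's own equivalence.** With treatment starting on the day of randomisation, a 16-week period ends on day 0 + 112 = 112, the assessment day. The label is then exact.

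**With a start on day d.** The 16-week period ends on day d + 112. Sixteen weekly sessions have 15 gaps, so session 16 falls on day d + 15 × 7 = d + 105. Days to spare for session 16 are 112 − (d + 105) = 7 − d.

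| Start day d | Session 16 on day | Days to spare before day 112 | 16-week period ends on day |
|---|---|---|---|
| 0 | 105 | +7 | 112 |
| 3 | 108 | +4 | 115 |
| 7 (latest notice) | 112 | 0 | 119 |
| 10 (assumed) | 115 | −3 | 122 |
| 14 (assumed) | 119 | −7 | 126 |

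At the article's own notice limit, the period overruns the assessment by 119 − 112 = 7 days. Counted by sessions, the course is complete by day 112 only if session 1 is held by day 7 and no week slips; a start on day 0 leaves room for one slipped week. The rows beyond day 7 are assumptions, since the text limits the time to notice and not the time to session 1.

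**With the 4-month wording.** The two follow-up times differ by 121.75 − 112 = 9.75 days. Assessment at day 121.75 would clear a 16-week course started on day 7 by 121.75 − 119 = 2.75 days. But the article also describes treatment as lasting four months, and a four-month period from day 7 ends on day 7 + 121.75 = 128.75, again seven days after the assessment. If treatment length and assessment time are the same number, the overlap equals the start delay, whichever unit is used.

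**The case against.** The strongest reply is that the schedule works as written. Sixteen weekly sessions span only 15 weeks, one week is an upper limit for notice and not a typical delay, and a start by day 7 puts session 16 no later than day 112. Participant convenience governs the time and venue of sessions that remain weekly, so it does not imply that weeks slip. Using 16 weeks and four months interchangeably is common shorthand. A journal article may leave assessment windows to the full protocol, and the SPIRIT figure is not shown. The trial tests no hypothesis, and its main outcome is recruitment and retention.

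Much of this stands. The session count does fit at its limit, the absence of a window in an article is not itself a fault, and the main outcome is untouched. What remains is a conflict between printed statements: a 16-week period that may begin a week after randomisation, an assessment 16 weeks after randomisation, and explicit wording that equates that time with the end of the intervention.

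A reader might go further and infer that most intervention participants would be assessed mid-therapy. If each weekly slot is held with an assumed probability of 0.95 or 0.90, starting on day 7, the chance that all 16 are held by day 112 is 0.95^16 = 44% or 0.90^16 = 19%. The documents do not support that use of the figures. The rates are assumed, and the inference requires every missed session to be made up later, which no section says. The attendance criterion and the topic guide's questions about missed sessions fit equally well with missed sessions simply being lost. A missed week then lowers attendance without moving the end of therapy. Half of the planned participants (40 of 80) are also in routine care and have no course to finish.

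Nor is there support for the idea that the attendance criterion is cut short at the follow-up visit: sessions are counted from session records and therapist logs.

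**Conclusion.** The point holds at moderate size. On the article's own figures, the end of a 16-week course can fall up to 7 days after the day-112 assessment, and 16 weekly sessions are complete by then only with a start by day 7 and no slipped week. A later first session, or sessions made up afterwards, would widen the overlap by an amount the documents do not fix. The follow-up time is also stated in two ways that differ by about 10 days.

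The consequence is confined to the intervention arm's follow-up scores and satisfaction ratings, some of which may be collected before therapy ends while being labelled end of intervention. No effect on a standard deviation, the choice of outcome or a sample size can be quantified from the documents. Recruitment, retention and attendance from session records are unaffected. Timing the assessment from randomisation in both arms is sound; the fault lies in equating that time with the end of treatment. The conclusion assumes that treatment starts only after notice of allocation.

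**What to change.** Reconcile the Procedure, Culturally adapted Getting Better Bite by Bite and Outcome assessment measures sections. Either of two changes is enough.

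1. **Move the assessment.** State one fixed time after randomisation, identical in both arms, that falls after the planned delivery period including the notice delay. On the 16-week and 7-day figures this means no earlier than day 119 (week 17), plus any further time allowed between notice and session 1. The cost is slightly longer follow-up per participant.
2. **Keep week 16.** Remove the end-of-intervention wording, report the number of sessions delivered by each participant's assessment date, and collect the intervention arm's CSQ-8 at actual therapy end. The cost is wording, one derived variable from records already kept, and a separate satisfaction contact for some participants.

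Under either option, use one unit, weeks or months, throughout. The treatment schedule itself is left to the investigators.

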**Fig. 2 Fig2:**
[figure not shown]
SPIRIT flow diagram

The Bulimic Investigatory Test, Edinburgh (BITE): The BITE is a self-rating scale comprising 33 items [20], divided into two subscales: the Symptom Scale with 30 items, measuring the extent of symptoms, and the Severity Scale with 3 items, indicating the severity based on the frequency of binge-eating and purging behaviors. The Symptom Scale items are answered in a yes/no format. Scoring ≥ 20 on the Symptom Scale indicates a highly disordered eating pattern and the presence of binge-eating, while a score of 10–19 suggests abnormal eating behavior like compulsive eating.

The Severity Scale, consisting of items 6, 7, and 27, investigates the frequency of fasting, purging, and binge-eating using a Likert scale. A score ≥ 5 suggests clinically relevant bulimic symptoms, and a score ≥ 10 indicates a high degree of severity. However, exceeding the Severity Scale threshold while staying within the normal range for the Symptom Scale does not lead to a diagnosis of BN; it may indicate the presence of psychogenic vomiting or laxative abuse without binge-eating.

The total score is obtained by summing the scores of both subscales. A total score > 25 indicates a potential case of binge eating. This questionnaire has been effectively used as a screening tool to identify binge-eaters in various countries [21].

Binge-Eating Disorder Screener (BEDS-7): The BED is a 7-item brief screening tool to screen Binge-Eating Disorder through 7 items [22]. The tool has previously been used on the Pakistani population, and the Cronbach's alpha coefficient obtained was 0.82 [23].

The Sick, Control, One, Fat, Food (SCOFF): The SCOFF [24] is a 5 item questionnaire consisting of three main domains of eating disorders which are (1) anorexia nervosa, (2) bulimia nervosa, or (3) other eating disorders. Each item marked as “yes” gets a score of 1 and summed up to get a cumulative score. Originally, a cut-off point of 2 or greater was established to achieve maximum sensitivity in detecting anorexia and Bulimia nervosa [24]. However, it has been recommended that a cut-off point of 3 offers the best balance between sensitivity and specificity. The tool has previously been used on the Pakistani population, though no Cronbach's alpha coefficients for the Pakistani population were determined [9, 25–27].

Eating Disorder Examination Questionnaire (EDE-Q): It’s a 28-item self-reported questionnaire adapted from the semi-structured interview to examine Eating Disorder. It is designed to evaluate the range and severity of features associated with a diagnosis of eating disorder using 4 subscales (Restraint, Eating Concern, Shape Concern and Weight Concern) and a global score. A cut-off of 4 on the global score is generally considered as clinically significant [28]. The scale has already been used on the Pakistani population, but the reliability coefficient was not calculated [25].

Kessler Psychological Distress Scale (KPDS): This 10-item questionnaire aims to assess psychological distress. The scale measures the emotional states with a 5 level response scale [29]. It has proven to be a reliable tool to administer to the Pakistani population as literature shows high reliability (0.89) for K-10 among the Pakistani Population [30].

Beck Scale for Suicide Ideation (BSS): To assess the frequency and intensity of suicidal thoughts, 21 item scales for suicidal ideation was developed by the Beck [31]. Each of the 19 items in the BSS is scored on a scale from 0 to 2, resulting in a total score ranging from 0 to 38, where higher scores indicate increased suicidal ideation. The BSS demonstrates favourable psychometric properties [31]. It has been used in the Pakistan previously [32], and the reported Cronbach's alpha for the Urdu translated version of the BSI were 0.75 [33] and 0.89 [32].

Beck Depression Inventory (BDI): The 29 item questionnaire of BDI [34] will be used to measure severity of depression. Score range of each item is 0–3 whereas severity ranges from minimally depressed (score lower than 13) to severely depressed (scores between 29 and 63). It is a globally validated tool to assess depression. The Urdu translation of the instrument showed a high Cronbach's alpha of 0.96 [32].

Oslo 3 Social Support Scale (O3SSS): O3SSS [35] will be used to assess the relationship with friends, family and neighbours. Each item in the instrument has a 5-point rating scale, resulting in a total score ranging from 3 to 15, where higher scores show stronger levels of support. The instrument has undergone validation in Urdu [36], and Cronbach's alpha for the Urdu version was 0.46 [37].

Client Satisfaction Questionnaire (CSQ-8): The CSQ will be used to assess the participants’ satisfaction with services received during the study [19].

### Qualitative component

A purposefully selected subset (stratified by age & gender) of participants (N = 15) in the intervention group will be invited to participate in a qualitative interview to explore their experiences and satisfaction with the intervention. Through a purposeful selection, we want to make sure that participants from all age brackets (both adults and middle-aged) and from both genders can participate in the qualitative interview.

A senior qualitative researcher will select the participants who will be independent of participants’ recruitment, intervention delivery, and response to treatment. The qualitative researcher will not have any information about participants' scores on assessment questionnaires and their responses to the intervention. This means that they will only be aware of basic demographic characteristics and not the assessment results. On average, interviews will last for 60 min.

The interviews will be either face-to-face or through telephone at a mutually agreed upon place and time by both the researcher and the participant.The interviews will be guided by a semi-structured topic guide. The topic guide will explore participants’ experience of participating in the intervention sessions including their feedback on content of the intervention and activities completed during sessions, perceived usefulness of the intervention, suggestions to improve the experience of participating in the intervention, feedback for therapists who delivered the intervention, challenges, and facilitators of participation in the intervention (Please see Appendix 1).All interviews will be audio recorded with the prior consent of the participants.

### Quantitative analysis

This is a pilot/feasibility study, therefore, the proposed study is not powered to detect between group differences. Our main outcome is the recruitment and retention of potential participants into the study. Consequently, we will report the recruitment and retention rates. Moreover, since the feasibility study does not aim to test differences or compare groups with formal hypothesis testing, we will report the outcome measures at both baseline and follow-up using appropriate descriptive statistics, measures of variability, and confidence intervals. Once the primary outcome measure for the full trial has been identified we will use the information provided in this study and a clinically meaningful difference to determine the effect size and corresponding sample size for the full trial. For this purpose, multiple measures of similar constructs are proposed to be administered where possible (e.g., eating disorders) to determine which measure to include in the definitive trial according to feasibility, acceptability, and sensitivity. In addition, the correlation of scores on different measures with severity of BED and/or BN will provide information about which measures are sensitive to change or congruent with the conceptual causal model of the intervention.

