### Objectives

The objectives of the proposed study are:To train master level psychologists in delivering Ca-GBBB intervention.To determine whether the intervention is acceptable for individuals who screen positive on measures of BN and BED and therapists delivering the intervention.To evaluate the feasibility of planned intervention.To identify barriers and facilitators of successful delivery of the intervention.To determine most suitable outcome measures for future RCTs.To gather preliminary data for the primary outcome measure to conduct a sample size calculation.

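### The only method named for sensitivity to change is a correlation of scores with severity, which shows convergent validity instead, and no severity reference is named or independent of the candidate measures

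*Protocol article*

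**What the plan says.** One objective of the protocol article (*Objectives*) is "To determine most suitable outcome measures for future RCTs". Under *Quantitative analysis*, several instruments for similar constructs are to be given, "to determine which measure to include in the definitive trial according to feasibility, acceptability, and sensitivity". The next sentence adds, as a further source, that "the correlation of scores on different measures with severity of BED and/or BN will provide information about which measures are sensitive to change", and ends "or congruent with the conceptual causal model of the intervention". The same section says of the outcome data that "we will report the outcome measures at both baseline and follow-up using appropriate descriptive statistics, measures of variability, and confidence intervals". No other analysis is tied to sensitivity to change.

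The section does not say which score stands for severity. Under *Outcome assessment measures* the eating-disorder instruments are BITE, BEDS-7, SCOFF and EDE-Q, each given at baseline and at 4 months. Two are described as measuring severity: the EDE-Q, and the BITE through "the Severity Scale with 3 items, indicating the severity based on the frequency of binge-eating and purging behaviors". For the BITE, "The total score is obtained by summing the scores of both subscales".

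**The concern.** Sensitivity to change concerns movement within a person, or a difference between arms, after something has happened. A correlation of scores with severity concerns whether people who stand high on one scale also stand high on another. The sentence offers the second as evidence for the first, and it refers to scores, not to change in scores.

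The reference is a further difficulty. Any listed eating-disorder score that could serve as severity comes from one of the instruments being compared. That instrument then cannot be judged on equal terms with the others.

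The stake is a stated objective. The section makes the size of the full trial depend on which primary outcome is identified, and on this component a measure that responds poorly could look good.

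**Working it through.** The documents attach no figure to this step, so there is none to reproduce. N = 80 (40 per arm) is the only number taken from them. SDs, correlations and effects below are assumptions.

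**1. What the correlation ignores.** For a score X, severity S and any constant c, Corr(X + c, S) = Corr(X, S). If every follow-up score in the group analysed fell by the same amount, or by nothing, the correlation would be the same. The mean change, which is the numerator of any responsiveness index, does not enter it.

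**2. Overlap, if the BITE Severity Scale is the reference.** Let the total be T = Y + V (Symptom plus Severity), k = SD(Y)/SD(V) and ρ = Corr(Y, V). Then r(T, V) = (1 + ρk) / √(1 + k² + 2ρk).

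| k | ρ = 0 | ρ = 0.5 |
|---|---|---|
| 1 | 1/√2 = 0.71 | 1.5/√3 = 0.87 |
| 2 | 1/√5 = 0.45 | 2/√7 = 0.76 |
| 3 | 1/√10 = 0.32 | 2.5/√13 = 0.69 |

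With ρ = 0 the whole correlation is overlap. With ρ = 0.5 overlap lifts it from 0.50 to between 0.69 and 0.87. EDE-Q, SCOFF and BEDS-7 have no such part-whole link with that scale. If the EDE-Q global score were the reference, its correlation with itself would be 1 and uninformative.

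**3. Can the two criteria disagree?** Assume severity S0 with SD 1, S1 = 0.7·S0 + √0.51·e − 0.5·G, where G = 1 in the intervention arm and arms are equal, so Var(G) = 0.25 and Var(S1) = 1 + 0.25 × 0.25 = 1.0625. All e are independent with SD 1.

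- Measure A (follows baseline level): A0 = 0.8·S0 + 0.6·e; A1 = 0.8·S0 + 0.6·e − 0.1·G.
- Measure B (noisier, responsive): B0 = 0.5·S0 + √0.75·e; B1 = 0.5·S1 + √0.75·e − 0.25·G.

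| | A | B |
|---|---|---|
| r with severity, baseline | 0.80 | 0.50 |
| r with severity, follow-up | 0.5725/√(1.0025 × 1.0625) ≈ 0.555 | 0.5625/1.0625 ≈ 0.53 |
| r of change with change in severity | 0.0125/√(0.7225 × 0.6625) ≈ 0.02 | 0.3625/√(1.7125 × 0.6625) ≈ 0.34 |
| Between-arm difference, baseline SDs | 0.10 | 0.5 × 0.5 + 0.25 = 0.50 |

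Correlation of scores favours A at both times; change favours B. This shows that a reversal is possible, not that it is likely for these instruments.

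**4. Precision.** For r = 0.5 and n = 80, Fisher's z gives 0.549 ± 1.96/√77 = 0.549 ± 0.223, a 95% CI of 0.31 to 0.65. With 60 completers (an assumption) it is 0.28 to 0.67. These intervals are for a single correlation. A difference between two correlations in the same people can be estimated more tightly.

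**The case against.** **The correlation is not the selection rule.** A reader might infer that the definitive outcome will be whichever measure has the highest correlation with severity. The text does not say that. Feasibility, acceptability and sensitivity are the criteria, the correlation is additional, and no ranking rule is written. This stands, so the point covers only the sensitivity-to-change component.

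**The sentence has a second purpose.** Congruence with the causal model can reasonably be examined by correlation. This also stands, and the correlation should be kept.

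**The timing is open.** A reader might infer a single-time, baseline-only correlation. The text does not fix the time, and both assessments are available. If change scores against change in severity were meant, the first difficulty would weaken. The text says scores, however, and the lack of an independent reference would remain.

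**Score correlations are not wholly uninformative about movement.** In the illustration A falls from 0.80 to about 0.555 while B goes from 0.50 to 0.53, and that pattern is a hint. It is indirect, the plan does not propose to read it, and it still misses a uniform shift.

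**Severity measures exist.** A reader might infer that severity is unmeasured or that every comparison is circular. Neither is supported. The BITE Severity Scale and the EDE-Q are on the list, and part-whole overlap affects only the BITE total. What remains is that the reference is unnamed and none of the listed options lies outside the candidate set.

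**The planned descriptives would allow change to be examined.** Means and SDs at both times give mean change over baseline SD. That is true, but the plan does not tie them to this purpose.

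**Conclusion.** The inference is wrong as written and should be corrected. A correlation of scores with severity does not establish sensitivity to change, yet it is the only method the protocol article names for that, and the severity reference is neither named nor independent of the candidates.

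The weight is moderate. Recruitment and retention, the main outcome, are untouched. The affected objective is the choice of outcome for the full trial, where the correlation is one input among several. The logical point needs no assumed numbers. The overlap figures assume the SD ratio and subscale correlation shown, and the reversed ranking rests wholly on assumed inputs. It shows only that the wrong measure could be favoured on this component. The documents do not support a claim that the wrong measure will be chosen.

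**What to change.** Under *Quantitative analysis*:

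1. Describe the correlation of scores with severity as evidence of convergent validity and of congruence with the causal model, and drop the claim about sensitivity to change.
2. Name the severity reference and the time point. Do not correlate the BITE total with its own Severity Scale; use the Symptom Scale if that comparison is wanted.
3. For sensitivity to change, report for each candidate (a) the standardised response mean (mean change divided by SD of change) by arm with 95% CI, and (b) the baseline-adjusted between-arm standardised difference with 95% CI. Both are descriptive, without testing.
4. Optionally, add the correlation of change with one pre-named anchor that is not a candidate, such as a participant-rated global change item.

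These estimates will be imprecise too. With 40 per arm, near zero effect the half-width is about 1.96/√40 = 0.31 for (a) and 1.96 × √(2/40) = 0.44 for (b) before any gain from baseline adjustment. They should inform judgement alongside feasibility and acceptability, not decide alone.

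The cost is a few sentences and a few descriptive estimates from the baseline and 4-month data already planned. Only the optional anchor would add a question at follow-up.
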